### Inpatient assessment

After eligibility is confirmed and consent obtained, the subject will be hospitalised for 1–2 weeks in Kitgum General Hospital for baseline assessments. The patients’ treatment will be updated per standard of care protocols. The clinical assessment will include a review of the pregnancy, birth and developmental history, the past medical history, a description of the progressive development of the symptoms of nodding syndrome, and the burden and types of seizures. A detailed physical assessment will also be performed including a neurologic, psychiatric and cognitive examination. The Gross Motor Function Classification System (GMFCS) and the Modified Rankin Scale will be used to describe gross motor abilities. The Mini-International Neuropsychiatric Interview for Children and Adolescents (MINI-KID) [26] will be used to document psychiatric disorders and the disorders classified per the Diagnostic Statistical Manual (DSM)-V criteria; Intellectual Disability will be assessed using the Child and Adolescent Intellectual Disability Screening Questionnaire (CAIDS-Q) [27]; nutritional status will be assessed against WHO 2000 anthropometric standards; cognitive function will be assessed using the Cogstate - a computerised cognitive testing program [28], and the quality of life (QOL) will be assessed using the Quality of Life in Childhood Epilepsy (QOLCE) questionnaire [29].

All participants not on standard of care treatments will be initiated on therapy including sodium valproate for seizures, nutritional, physical and psychological therapy as appropriate. Patients receiving current standard of care treatment but with ongoing seizures will have their doses of sodium valproate optimised to 20-35 mg/kg/day.

Five-10mls of blood will be drawn for standard of care testing (full blood count, liver and renal function tests, and HIV). We will also obtain skin snips for *O.volvulus* microfilaria density (on microscopy and Real Time [RT] PCR) and *Wolbachia* load testing. Lumbar puncture will be performed and 3-4mls of cerebrospinal fluid obtained. Aliquots of plasma, serum and cerebrospinal fluid will be stored for baseline evaluation of study specific tests.

All will have a 30-min diagnostic electroencephalographic (EEG) recording. In addition, an overnight EEG will be obtained in a convenient sample of 45 participants selected by stratified random sampling to reflect the five clinical stages of nodding syndrome [30].

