### Follow period and study outcome determination

Study participants will be re-evaluated at 6, 12, 18 and 24 months. Only clinical assessments will be performed at 6, 12 and 18 months. At 24 months, however, participants will again be hospitalised for one week for inpatient observation and testing, during which all the pre-randomisation procedures and tests will be repeated to determine study outcomes.

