### Assessment of efficacy and safety

#### Primary efficacy outcome

The objective of the trial is to determine if targeting *O.volvulus* through drugs which kill *Wolbachia* can modify the pathogenic processes in nodding syndrome. We will therefore investigate the effects of doxycycline compared to placebo on the presence and titres of serum antibodies to HNPs (identified in the concurrent case-control study) or leiomodin and on inflammatory markers, the microfilaria density and *Wolbachia* load. The primary efficacy measure will be the proportion patients testing positive for and levels or titres of antibodies to HNPs or leiomodin at 24 months.

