### Statistical analysis

Analysis will be by intention to treat. The analysis will compare the proportions of patients testing positive for and the levels or titres of antibodies to HNPs or leiomodin at baseline and at 24 months in both arms. Both crude (unadjusted) and adjusted effect estimates will be computed. The chi square test will be used to compare proportions of children with the different antibodies in the two arms; the Students t-test will be used for means of normally distributed data and the Mann-Whitney U test for skewed data. We will also determine the mean change or reduction in the levels or titres of the antibodies and inflammatory markers with the intervention. Time to event (e.g. to seizure resolution) will be measured from the date of randomisation using Kaplan Meyer Survival analysis and by Cox regression analysis. For the cognitive tests, in addition to classification as impaired or not (in comparison to norms determined from unaffected sibling controls in the concurrent case control study), we will also measure mean improvements in scores. The rates determined will be adjusted for age, HIV infection, weight for height z scores and corrected for multiple testing. We will examine safety (serious adverse events and adverse events) and assess compliance and the factors for poor compliance.

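### No antibody analysis is specified as adjusted for the baseline antibody result, so precision may be lost; the planned crude comparison remains valid and adequately powered

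*Protocol article*

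**What the plan says.** Under Primary efficacy outcome, the protocol article defines the endpoint as the proportion positive for, and the "levels or titres of antibodies to HNPs or leiomodin at 24 months".

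Under Statistical analysis it names the tests. For positivity: "The chi square test will be used to compare proportions of children with the different antibodies in the two arms". For levels, a t-test or a Mann-Whitney test, depending on skewness. It then promises that "Both crude (unadjusted) and adjusted effect estimates will be computed", and the only covariates named anywhere are in this sentence: "The rates determined will be adjusted for age, HIV infection, weight for height z scores and corrected for multiple testing".

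Baseline antibody results are to be available. Inpatient assessment says that plasma, serum and cerebrospinal fluid are "stored for baseline evaluation of study specific tests". The follow-up section says that at 24 months "all the pre-randomisation procedures and tests will be repeated to determine study outcomes". Statistical analysis itself refers to "antibodies to HNPs or leiomodin at baseline and at 24 months in both arms", and says the team will also "determine the mean change or reduction in the levels or titres of the antibodies". Mean change in level is listed among the secondary outcomes.

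Randomisation is stratified by skin-snip result, not by antibody status.

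**The concern.** About half the participants are expected to be antibody-positive at entry. If positivity tends to persist, a participant's baseline result says a good deal about the 24-month result, probably more than age, HIV infection or weight-for-height. A model that adjusts for those three and not for the baseline outcome would leave explainable variation in the error term. It would also leave a chance difference between arms in baseline positivity uncorrected, and nothing in the randomisation balances that factor directly.

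The planned mean change does not fill the gap. It does nothing for the proportion positive. For levels it is less precise than regression on baseline whenever the correlation is below 1, and less precise than the 24-month value alone when the correlation is below 0.5.

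**Working it through.** **Inputs from the protocol article (Sample size):** 50% positive at baseline; 50% v 30% positive at 24 months; 80% power; 5% significance, taken as two-sided; 10% loss; 230 participants, 115 per arm.

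**Assumed:** the link between baseline and 24-month status. The documents give no figure, so a range is shown.

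**1. The plan's own figure.** The two-proportion formula with pooled variance under the null is

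n = [1.96·√(2·0.4·0.6) + 0.842·√(0.5·0.5 + 0.3·0.7)]² / 0.2² = 93 per arm.

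The continuity correction gives (93/4)·[1 + √(1 + 4/(93·0.2))]² = 102.8, so 103. Allowing for 10% loss, 103/0.9 = 114.4, so 115 per arm and 230 in total. The stated size reproduces exactly.

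**2. Power of the planned crude test.** With 103 evaluable per arm, the uncorrected chi-square has about 84% power by the normal formula and about 85% by simulation. Both exceed the stated 80%.

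**3. Chance imbalance.** The standard error of the between-arm difference in baseline positivity is √(2·0.5·0.5/103) = 0.070, or 7.0 points; the 95% range is ±1.96·7.0 = about ±13.7 points. Without a treatment effect, an imbalance carries into the 24-month difference multiplied by (persistence − conversion). Persistence is the share of baseline positives still positive at 24 months, and conversion the share of baseline negatives who become positive. At 80%/20%, a 10-point imbalance becomes 10·(0.8 − 0.2) = 6 points; at 60%/40%, 2 points; with no correlation, none.

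**4. Power after stratifying on baseline status.** Simulated trials, 103 per arm, 50% positive at baseline. The placebo arm follows the persistence/conversion rates shown, and doxycycline multiplies each rate by 0.6, which gives 50% v 30% overall. The crude chi-square is compared with a Cochran-Mantel-Haenszel test stratified by baseline status. With half positive at baseline, the correlation in the placebo arm equals persistence minus conversion.

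| Persistence / conversion (assumed) | Correlation | Crude power | Stratified power |
|---|---|---|---|
| 50% / 50% | 0 | 85% | 84% |
| 60% / 40% | 0.2 | 85% | 85% |
| 70% / 30% | 0.4 | 85% | 88% |
| 80% / 20% | 0.6 | 85% | 93% |
| 90% / 10% | 0.8 | 85% | 98% |

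With a common conditional odds ratio in place of a common risk ratio, the stratified figures are about the same or up to two points higher. Type I error of the stratified test is about 5% throughout; that of the crude test is 4.5–4.7%.

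**5. Levels.** Let r be the correlation between baseline and 24-month level, with equal variances and roughly continuous values. Relative to the variance of the 24-month value, regression on baseline gives 1 − r² and the change score gives 2(1 − r). Their ratio is (1 − r²)/[2(1 − r)] = (1 + r)/2.

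| r (assumed) | Regression v 24-month value | Change score v 24-month value | Regression v change score |
|---|---|---|---|
| 0.3 | 0.91 | 1.40 | 0.65 |
| 0.5 | 0.75 | 1.00 | 0.75 |
| 0.7 | 0.51 | 0.60 | 0.85 |

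**The case against.** The strongest reply is that nothing in the planned analysis is wrong. An unadjusted comparison of randomised arms is unbiased and holds its type I error, and chance imbalance is already reflected in its standard error. This stands.

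A reader might go further and infer that the omission leaves the trial underpowered, especially as the protocol expects a weaker effect in established patients. The documents do not support that. The drop from 50% to 30% already is the weaker effect (the stronger one, for new-onset patients, was 50% to 25%). The 230 participants were sized for it, and the crude test exceeds the stated power.

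Four further limits also stand:

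- **Scope of the covariate sentence.** It follows the sentence on cognitive tests and speaks of rates, so it may not govern the antibody outcome. If it does not, the antibody covariates are unstated, which a condensed article may leave to the analysis plan. On either reading, no baseline-antibody adjustment is specified.
- **Availability.** It is tempting to say that every participant has a baseline result for every antibody. Laboratory testing makes the cell-based assays depend on immunohistology, and some target proteins are still to be identified in the case-control study.
- **Use of baseline.** It is not ignored: antibodies are compared at both times and mean change is analysed.
- **Levels.** With about half the participants antibody-negative, many values may lie at the detection limit. The variance factors above then do not carry over directly.

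A reader might also suspect that weight-for-height, itself an outcome, would enter as a post-randomisation value. Nothing says so: nutritional status is assessed at baseline, and naming the time point is ordinary analysis-plan detail.

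**Conclusion.** The point holds as one about efficiency. The article names unadjusted tests and one covariate set, and neither uses the baseline value of the primary outcome, for which samples are stored before randomisation. The price is lost precision and chance imbalance left in the estimate. It is not bias, an inflated error rate or a shortfall against the stated power.

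For positivity, the change in power from adjustment runs from about −1 to +13 points (85% to between 84% and 98%) and becomes material only if positivity persists in most participants. For levels, adjustment would remove 9% to 49% of the variance of the 24-month value at r = 0.3 to 0.7, if levels behave roughly continuously. Both ranges rest on an assumed correlation, so the existence of a gain under reasonable persistence is well supported but its size is not.

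**What to change.** Prespecify, before unblinding:

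- **Positivity.** As the primary adjusted estimate, a Mantel-Haenszel or standardised risk difference stratified by baseline positivity for the same antibody. This keeps the difference in proportions on which the trial is sized; the odds ratio from a baseline-adjusted logistic model would not, unless standardised back to risks.
- **Levels.** Regress the 24-month level on the baseline level, transformed if skewed, with a rank-based or censored version if many values lie at the detection limit.
- **Crude tests.** Keep them as sensitivity analyses.
- **Scope.** State which outcomes the covariate sentence covers.
- **Missing baseline results.** Give a rule for participants without a baseline result for a given antibody.

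The cost is wording and slightly more analysis work. No additional participants or visits are needed, as baseline sampling and testing are already planned. The statistical downside is a power loss of about one point if baseline and 24-month status turn out to be uncorrelated.

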## Background

Nodding syndrome is a complex neurolo**g**ical disorder of unknown aetiology. The disease burden is unknown but it is estimated that there are about 10,000 affected children in eastern and central Africa. Of these, about 3000 live in Northern Uganda [1, 2].

The first reports of nodding syndrome came from Tanzania in the 1960’s [3]. Subsequent cases were reported from Liberia [4], South Sudan [5–7] and Uganda [8, 9]. The disease affects previously normally developing children characterized by bouts of repetitive head nodding (the pathognomonic feature). Symptoms develop in children between the ages of three and 18 years, and initially, the head nodding occurs in association with feeding, a cold breeze or cold weather [7, 10, 11]. Over the years however, this is complicated by multiple types of seizures, malnutrition, cognitive and physical decline [1, 7, 10, 12].

There have been many studies of environmental, infectious, toxic and genetic factors to determine aetiology but the cause remains unknown to date [13–15]. On the other hand, a consistent epidemiologic association has been documented between nodding syndrome and infection with *Onchocerca volvulus* (a filarial nematode) [6, 10, 12, 13, 15]. This parasite has previously also been associated with the *Nakalanga* syndrome (a tropical syndrome characterised by short stature and malnutrition) [16–18]. *O.volvulus* has in addition been associated with generalised epilepsy [19]. However, *O.volvulus* is endemic in many parts of Africa, Latin America and Asia where it causes corneal keratitis (river blindness) but nodding syndrome has only been reported in parts of Africa. *O. volvulus* has also not been observed in brain tissue. If *O. volvulus* is involved in the aetiology of nodding syndrome, alternative mechanisms other than direct parenchymal injury are likely.

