### Participants

Participants will be children and adolescents with confirmed nodding syndrome as defined by the WHO [25] i.e. A child who has experienced head nodding on two or more occasions, observed by a trained health worker or documented on EEG, with symptom onset between the ages of three and 18 years, plus any one of 1) triggered by food or cold weather; 2) presence of other seizures or neurological abnormalities and cognitive decline; 3) clustering in space or time in the local population.

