### Sample size

From our pilot studies, ~ 50% of patients with prevalent nodding syndrome had antibodies to a HNPs and ~ 60% to leiomodin [2, 22]. We hypothesise that among patients with new onset nodding syndrome (symptoms < 12 months), six weeks’ therapy with doxycycline will cause a 50% reduction in the proportion of patients with and the levels or titres of antibodies to HNPs (a reduction from 50 to 25% compared to placebo) at 24 months. In Uganda, however, there has been no incident cases of nodding syndrome since 2014. It is anticipated that the intervention may not be as efficacious in patients with established symptoms (i.e. patients with symptoms ≥12 months) and the effect on antibodies would be smaller (an anticipated 40% reduction from 50 to 30%). To demonstrate this effect at 80% power and 5% level of significance and allowing for 10% losses to follow up, we will need to recruit a total of 230 patients with established symptoms (115 in either arm).

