## Discussion

The goal of this study is to understand the pathogenesis of, and to develop specific interventions for, nodding syndrome. Currently, there is no specific treatment for nodding syndrome. The only available treatment is a package of therapies aimed at symptomatic relief [32]. This project has the potential to advance the understanding of nodding syndrome, allow definitive diagnosis and gain insight into potential new approaches for treatment and prevention. If evidence of neuro-inflammation is found and/or specific autoantibodies, immune-modulatory therapies, for example with high dose steroids, may be considered at symptom-onset [2]. In addition, a biologic association between nodding syndrome and *O.volvulus* would allow escalation of treatments and prevention. If a potential use for doxycycline, as treatment for nodding syndrome is observed, it would also be a proof of principle that treatment is possible in older children. Such a strategy could also be explored for younger newly affected children. It is important to point out that the proposed use of doxycycline is based on its effectiveness as treatment for adult *O. volvulus.* Its success will not depend on *Wolbachia* playing a direct role in the pathogenesis of NS (although it may), rather, it is a test of the broader hypothesis that *O.volvulus* plays a role in the pathogenesis of NS.

The approach of using doxycycline is supported by the facts that (1) *O.volvulus* infection has had the most consistent association with nodding syndrome out of many potential risk factors examined to date [33]; (2) doxycycline is a cheap and safe drug and the only curative treatment for adult *O.volvulus* currently available [23]; (3) a direct intervention has considerable advantages over epidemiological association studies in elucidating causality. This is thus a low risk but potentially high gain approach: a positive result would have great significance in understanding both pathogenesis and offering a hope of treatment, whilst a negative result would still be helpful in indicating that whatever the pathogenesis, a simple approach to reducing *O.volvulus* load may not necessarily offer an advantage.

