The trial has as one of its major strengths - the dual benefit of potentially determining both the pathogenesis of nodding syndrome and providing a specific treatment intervention. This is supported by the use of both clinical and laboratory biomarkers either as primary or secondary outcome measures. The main weakness is that with the decline in incident cases who would potentially register most improvements with treatment, the study will have to rely on patients with established symptoms in whom, probably lower degrees of improvements will be observed.

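### The adjusted analysis lists age but not years since onset of head nodding, which the protocol itself ties to decline; adding it is a cheap, modest precision gain, mainly for clinical outcomes

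*Protocol article*

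**What the plan says.** The Statistical analysis section promises two sets of results: "Both crude (unadjusted) and adjusted effect estimates will be computed". It then names what the adjustment contains: "The rates determined will be adjusted for age, HIV infection, weight for height z scores and corrected for multiple testing". Time since onset does not appear there, and the Randomisation section stratifies on skin snip result only.

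Elsewhere the article treats length of illness as important. On the course of the disease after the first head nodding, the Background says: "Over the years however, this is complicated by multiple types of seizures, malnutrition, cognitive and physical decline". The Sample size section separates recent from established illness at 12 months and plans for established cases.

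The information needed should be available. The case definition under Participants requires a case "with symptom onset between the ages of three and 18 years", so age at onset has to be established for each participant. The Inpatient assessment section adds a history of how the symptoms developed.

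**The concern.** A covariate improves an adjusted analysis to the extent that it predicts the outcome. On the protocol's own description, years of illness should predict several 24-month outcomes: seizure freedom, GMFCS level 3–5, psychiatric disorder on the MINI-KID, intellectual disability on the CAIDS-Q, and cognition. Most of these are proportions at 24 months and not change scores, so they carry accumulated disease directly.

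Age stands in for duration only in part. Two 16-year-olds with onset at 3 and at 14 have been ill for 13 and 2 years. Weight-for-height picks up some of the same signal, because malnutrition is among the accumulating effects, but it does so indirectly.

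At stake is the width of the intervals, chiefly for the clinical outcomes. Treatment is randomised, so leaving the variable out does not distort the comparison.

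**Working it through.** **The plan's own figure.** For 50% against 30%, two-sided 5%, 80% power, mean proportion 0.40:

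- n per arm = (1.96·√(2·0.40·0.60) + 0.8416·√(0.25 + 0.21))² / 0.20² = 93.
- With continuity correction: (93/4)·(1 + √(1 + 4/(93·0.20)))² = 102.8, so 103.
- With 10% loss: 103/0.9 = 114.4, so 115 per arm and 230 in total. This reproduces the stated size, and the present point leaves it unchanged.

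**How much of duration does age carry?** The document gives no distributions. Assume that onset age and duration are independent, each with an SD of 2 to 4 years. As age = onset age + duration, the share of duration's variance explained by age is

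c = SD²(duration) / [SD²(onset) + SD²(duration)].

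- SD 2 for duration and 4 for onset: 4/20 = 20%.
- Equal SDs: 50%.
- SD 4 for duration and 2 for onset: 16/20 = 80%.

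**Continuous clinical outcomes.** Let R be the share of outcome variance explained by duration (assumed 10–30%), with age acting only through duration. Age alone leaves 1 − Rc unexplained; age plus duration leaves 1 − R. The equivalent gain in sample size is (1 − Rc)/(1 − R) − 1 = R(1 − c)/(1 − R).

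| R | c = 30% | c = 50% | c = 70% |
|---|---|---|---|
| 10% | 7.8% | 5.6% | 3.3% |
| 20% | 17.5% | 12.5% | 7.5% |
| 30% | 30.0% | 21.4% | 12.9% |

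With the extreme values of c the range widens slightly: 0.10·0.20/0.90 = 2.2% to 0.30·0.80/0.70 = 34.3%. If R is zero, so is the gain.

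**Binary outcome at the planned effect (50% against 30%, 103 evaluable per arm).** The unadjusted SE of the risk difference is √(0.46/103) = 0.0668. Simulation with logistic adjustment, 206 participants and 1,500 runs per row; the SE is that of the standardised risk difference:

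| Odds ratio per SD of duration | Age–duration correlation | SE, age only | SE, age + duration | Power, age only | Power, age + duration |
|---|---|---|---|---|---|
| 1.0 | 0.3 | 0.0660 | 0.0661 | 83.4% | 83.3% |
| 1.0 | 0.7 | 0.0669 | 0.0671 | 83.7% | 83.7% |
| 1.5 | 0.3 | 0.0672 | 0.0658 | 83.5% | 84.3% |
| 1.5 | 0.7 | 0.0656 | 0.0654 | 85.8% | 85.5% |
| 2.0 | 0.3 | 0.0660 | 0.0631 | 85.0% | 88.1% |
| 2.0 | 0.7 | 0.0642 | 0.0629 | 85.1% | 86.9% |
| 3.0 | 0.3 | 0.0667 | 0.0601 | 83.2% | 90.1% |
| 3.0 | 0.7 | 0.0637 | 0.0601 | 88.1% | 90.4% |

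Power changes by about 0 to 7 points. When duration is irrelevant, adding it costs almost nothing.

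**Could the trial show how the effect varies with duration?** Take a median split (51.5 per cell) and the protocol's own contrast, risk differences of 25 and 20 points.

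- SE = √((0.25 + 0.1875 + 0.25 + 0.21)/51.5) = 0.132.
- Power = Φ(0.05/0.132 − 1.96), about 6%.
- For 80% power: (1.96 + 0.8416)²·0.8975/0.05², about 2,800 per cell.

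**The case against.** The strongest reply is that nothing here is an error. Age, HIV infection and weight-for-height are plausible covariates, crude estimates will be given beside adjusted ones, and the analysis plan is not shown. The covariate sentence follows one on cognitive tests and speaks of rates, so its scope is unclear, and the tests named for the main comparisons are unadjusted. This stands as a limit on the weight of the point. It does not remove it, because the article names a specific list and the suggestion concerns that list.

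The size is also open to attack. The SDs and R values are assumed. The variance formula is for linear models; in a logistic or Cox model a prognostic covariate does not narrow the interval for the log ratio, and the gain appears as power. Cogstate and growth are also analysed as mean changes, which already remove much of the accumulated deficit. Any adjustment for the baseline value of an outcome would likewise leave less for duration to explain. All of this stands.

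Stronger readings are tempting, and the document does not support them:

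- **A gradient of drug effect with years of illness.** The Sample size section says "It is anticipated that the intervention may not be as efficacious in patients with established symptoms (i.e. patients with symptoms ≥12 months", and the Discussion repeats that "the study will have to rely on patients with established symptoms in whom, probably lower degrees of improvements will be observed". Both rest on one split at 12 months. The planned participants all lie on the established side, and no trend beyond it is claimed.
- **Clinical stage as a predictor of response.** Stage appears only as the sampling frame for 45 overnight EEGs and is never linked to response.
- **A planned read-across to new cases.** The Discussion says only "Such a strategy could also be explored for younger newly affected children". That suggests further research; it does not draw an inference.

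**Conclusion.** The point holds as a modest improvement in efficiency. On the protocol's own account years since onset is prognostic for clinical outcomes, it should be obtainable at baseline, and age replaces it only in part.

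For continuous clinical outcomes the gain is about 3–30% in equivalent sample size, assuming that duration explains 10–30% of the variance and age captures 30–70% of that share. For the antibody primary outcome it is unknown and may be nil, since the Background links years of illness to clinical decline and not to antibody positivity. The simulated 0 to 7 points of power depend on the assumed odds ratio. The sample size of 230 is not in question.

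A reader might infer that the treatment comparison is biased, or that adding duration would show what doxycycline does in newly affected children. Neither follows. Randomisation protects the comparison. A covariate main effect gives no estimate by duration, and an interaction would have about 6% power for the protocol's own contrast. With no incident cases in Uganda since 2014, it would also extrapolate below the durations observed.

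**What to change.** Add years from onset of head nodding to randomisation, as a continuous variable, to the covariates in the Statistical analysis section. Say which outcomes the adjusted models cover, chiefly the 24-month clinical ones: seizure freedom, GMFCS 3–5, MINI-KID, CAIDS-Q and cognition. For binary outcomes report standardised risk differences, or describe the expected benefit as power, since the odds-ratio interval will not show it.

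A single treatment-by-duration estimate with a 95% CI is optional. If included, label it exploratory and do not use it to support statements about newly affected children.

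The cost is wording only, with no new data or visits. The small downside is that recalled age at onset is imprecise. That shrinks the gain, but it does not bias a randomised comparison, provided the variable is fixed before randomisation.
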